### Follow-up

The goal of follow-up is to evaluate the long-term efficacy of acupuncture on pain relief. The follow-up assessments will be performed after treatment and will last for 3 months. During the follow-up period, patients will continue to maintain pain diaries and complete the questionnaires. They can submit the relevant information to researchers via email or short message service. Researchers will also pay close attention to changes in patient illness.

### Randomization and blinding

One hundred and six eligible patients will be randomly assigned to either the treatment group or the control group in a 1:1 ratio after all baseline assessments. The random allocation sequence was generated by a computer. A researcher who does not participate in treatment, data collection and evaluation will provide the random number and group assignment to each center. The randomization is blinded and allocation is hidden. Owing to the unique nature of the acupuncture operation, it is impossible for the acupuncturists to be blinded. However, patients, the data collector and the statistician will be blinded.

### Sample size calculations and statistical analysis

This trial will use a clinical-superiority design that aims to verify that the curative effect of acupuncture is better than that of comfort needles. The primary outcome measure is proposed to be the VAS. The minimal important difference (MID) for improvement on the VAS was found to be − 3.9 cm and/or − 49% [20]. According to our pre-experimental treatment of women with pain related to endometriosis, assuming the standard deviation (SD) to be 1.7 and the difference between two treatment effect to be 3, the statistical power is 80% and the significance level is 0.05. According to the formula [21]:$$ N=2\times {\left[\left({Z}_{1-\alpha }+{Z}_{1-\beta}\right)/\left(\delta -{\delta}_0\right)\right]}^2\times {S}^2, $$

where *N* represents size per group, *Z*_1-α_ is Type I error, *Z*_1-β_ is Type II error, *δ* is expected SD of the population being sampled, *δ*_0_ is tolerable error in distance from mean value and *S*^2^ is SD. So it requires each group to contain no less than 44 patients. With an estimated 20% dropout rate, we plan to recruit 53 patients for each group, for a total of 106 patients.

Data will be summarized with counts for categorical variables present as mean and SD for normally distributed variables, or median (interquartile) for the variables not normally distributed. Missing data will be imputed according to the last-observation-carried-forward (LOCF) [22] principle. The data will be subjected to intent-to-treat analysis. A statistician blinded to the group settings will perform the statistical analysis. The between-group difference will be compared by analysis of covariance. The variables not normally distributed will be assessed by the rank-sum test. If participants have taken analgesics during the trial, they will be excluded from the analysis and the rate difference of outcomes between the two groups will be analyzed. Statistical significance will be set at *P* < 0.05.

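### The trial is sized on a non-zero superiority margin that is never given a value, while the only stated decision rule is an ANCOVA at P < 0.05 with no margin

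*Protocol article*

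**What the plan says.** Everything relevant is in the section on sample size calculations and statistical analysis of the protocol article.

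- **Design:** "This trial will use a clinical-superiority design that aims to verify that the curative effect of acupuncture is better than that of comfort needles".
- **Sizing inputs:** "assuming the standard deviation (SD) to be 1.7 and the difference between two treatment effect to be 3", and "the statistical power is 80% and the significance level is 0.05". Units are not given; cm is assumed here, from the 10-cm VAS.
- **Formula:** N per group = 2 × [(Z₁₋α + Z₁₋β)/(δ − δ0)]² × S². The legend calls δ an expected SD. Its entry for δ0 reads "is tolerable error in distance from mean value and", with no number attached. The stated result is 44 per group, raised to 53 (106 in total) for dropout.
- **Important difference:** "The minimal important difference (MID) for improvement on the VAS was found to be" −3.9 cm and/or −49%.
- **Analysis:** "The between-group difference will be compared by analysis of covariance", with a rank-sum test for variables that are not normally distributed. The threshold is "Statistical significance will be set at *P* < 0.05". No margin, shifted null or confidence-limit criterion is attached to either test.

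**The concern.** A formula with (δ − δ0) and a one-sided Z₁₋α belongs to a superiority-by-margin test, where the null hypothesis is that the difference does not exceed δ0. Together with the label of clinical superiority, it implies that the trial is meant to show a benefit larger than some minimum. An ANCOVA judged at P < 0.05 with no margin asks only whether the difference is zero.

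The two questions can have different answers in the same data. A result between the two thresholds would succeed under the written rule and fail under the hypothesis used to size the trial. With δ0 unstated, nobody could say afterwards which conclusion the plan had allowed.

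**Working it through.** **Inputs.** SD 1.7, assumed difference 3, power 80%, α 0.05, 44 per group before and 53 after the dropout allowance (all from the protocol article). Differences are written as positive benefits in cm. The SD of 1.7 is taken as that of the unadjusted outcome.

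**1. Reproduce the stated 44.** With |δ − δ0| = 0.9 and one-sided α:

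2 × (1.645 + 0.842)² × 1.7² / 0.9² = 35.74 / 0.81 = 44.1

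With z-values cut to 1.64 and 0.84 it is 2 × 2.48² × 2.89 / 0.81 = 43.9, which rounds up to 44.

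**2. Try a zero margin.** With δ = 3 and δ0 = 0:

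- one-sided: 35.74 / 9 = 3.97, so 4 per group
- two-sided: 45.37 / 9 = 5.04, so 6 per group

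A zero margin cannot give 44.

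**3. Solve for the implied gap at 44.**

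- one-sided: √(35.74 / 44) = 0.90
- two-sided: √(45.37 / 44) = 1.02

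If δ is the assumed 3, then δ0 is 3 − 0.90 = 2.10 or 3 − 1.02 = 1.98. A gap of 0.9 also equals 3.9 − 3, so 3.9 may have entered as δ or as δ0. The document does not say which.

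**4. What the written rule requires.** The standard error is 1.7 × √(2/n): 0.362 at 44 per group and 0.330 at 53. The smallest significant observed difference, two-sided 5% against zero, is:

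| n per group | t × SE | Unadjusted | ANCOVA, assumed baseline correlation 0.3 to 0.7 |
|---|---|---|---|
| 44 | 1.988 × 0.362 | 0.72 cm | 0.69 to 0.51 cm |
| 53 | 1.983 × 0.330 | 0.65 cm | 0.62 to 0.47 cm |

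A true difference of 1 cm would give P < 0.05 with probability of about 79% (44 per group) or 86% (53 per group) by the normal approximation, without baseline adjustment.

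**5. What a margin test would require at 44 per group.**

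- δ0 = 2.1, one-sided: 2.1 + 1.645 × 0.362 = 2.70 cm
- δ0 = 2.0, two-sided: 2.0 + 1.960 × 0.362 = 2.71 cm

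**6. Power of a margin test if the true difference is 3 cm.**

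| δ0 | n per group | One-sided 5% | Whole 95% CI beyond δ0 |
|---|---|---|---|
| 2.1 | 44 | 80% | 70% |
| 2.1 | 53 | 86% | 78% |
| 3.9 | 44 or 53 | essentially 0 | essentially 0 |

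In the last row the assumed effect lies below the margin.

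**The case against.** The strongest reply is that the protocol never says a P-value below 0.05 will be reported as clinical superiority. The design sentence explains its own term as being better than comfort needles, which an ordinary test of zero can address, and the Objective and Discussion speak only of efficacy and safety. This stands. A reader might infer that every significant result will be presented as clinically superior, but the document does not support that.

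A reader might also set 0.7 cm against the cited 3.9 cm and call the rule several times too lenient. The 3.9 cm is quoted for improvement on the VAS. That reads most naturally as a change within patients, and it is not shown to be a threshold for a difference between group means. It should not serve as the yardstick without justification, so the comparison here is with the assumed 3 cm and with the margin implied by 44 per group.

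Third, the zero null is itself inferred, and a full analysis plan that is not shown might specify a shifted one. That is possible. But the article fixes a design label, a formula, a test and a threshold, and these do not agree on their face.

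Finally, δ and δ0 are mislabelled, so the defect could be seen as one of sample size alone. The two are linked, but correcting the count would still leave open what the test may conclude. If the label means only ordinary superiority, then δ0 is zero and the derivation of 44 falls.

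**Conclusion.** The point holds as an inconsistency between stated elements. The sample size rests on a non-zero δ0 of unstated value, and the written decision rule uses no margin. At SD 1.7 cm the rule is met at about 0.65 to 0.72 cm (53 and 44 per group, two-sided, unadjusted), which is under a quarter of the assumed 3 cm. A margin test consistent with 44 per group and δ = 3 would need about 2.7 cm.

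The figures assume cm units, the stated SD and the ordinary zero null of an ANCOVA. The 2.7 cm further assumes that δ is the assumed difference of 3. The back-calculated δ0 of 2.0 to 2.1 is an inference, not a value in the plan. The between-group comparison itself remains valid; what needs settling is which claim it can support.

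**What to change.** Before unblinding, and while the trial is still recruiting as its status section says, state δ, δ0 and the sidedness of the test, and correct the symbol definitions. Report the baseline-adjusted VAS difference with its 95% CI. Then choose one route:

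- **(a) Keep clinical superiority.** Claim it only if the whole 95% CI lies beyond the declared δ0, and restate the power at that margin. This rule corresponds to one-sided 2.5%, so the power is lower than the one-sided 5% formula suggests. It is essentially nil if δ0 = 3.9 and δ = 3.
- **(b) Make it ordinary superiority.** Drop the word clinical and δ0, conclude from P < 0.05 only that acupuncture is superior to comfort needles, and restate the sample-size justification for a zero null with the planned 106. For orientation, the difference detectable with 80% power (two-sided) is (1.960 + 0.842) × SE: 1.02 cm at 44 per group and 0.93 cm at 53.

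A comparison of the proportions reaching the cited 3.9 cm and/or 49% improvement could be added, but it is optional.

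Route (b) needs only text changes. Route (a) needs no new data, but whether 106 patients suffice depends on the δ0 declared. Either way the published sample-size derivation must be corrected, and a small significant difference could not be called clinical superiority.

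### The 44 per group does not follow from the stated difference of 3 and SD of 1.7, δ0 has no value, and the 80% power has no stated hypothesis to which it applies

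*Protocol article*

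**What the plan says.** Everything relevant is in the section on sample size calculations and statistical analysis of the protocol article.

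- Aim: "This trial will use a clinical-superiority design that aims to verify that the curative effect of acupuncture is better than that of comfort needles".
- Reference value: "The minimal important difference (MID) for improvement on the VAS was found to be" 3.9 cm and/or 49%, as a reduction.
- Inputs: "assuming the standard deviation (SD) to be 1.7 and the difference between two treatment effect to be 3, the statistical power is 80" per cent, with a significance level of 0.05.
- Formula: N = 2 × [(Z₁₋α + Z₁₋β)/(δ − δ0)]² × S², with N the size per group. The key calls δ an expected SD, δ0 a tolerable error and S² an SD. No value is given for δ0.
- Result: "So it requires each group to contain no less than 44 patients". This becomes 53 per group and 106 in total for 20% dropout.
- Analysis: "The between-group difference will be compared by analysis of covariance", with significance at P < 0.05. No margin is named and sidedness is not stated.

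**The concern.** The section prints inputs, a formula and a result, so the result can be checked, and it does not follow. A difference of 3 with an SD of 1.7 is a standardised effect of about 1.8, which needs a handful of patients per group. The stated 44 is 7 to 11 times larger.

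The gap can only come from δ0, the term that turns the formula into a test against a margin. That term has no number, and its description does not describe a margin. A reader cannot tell whether 80% power refers to showing any difference or to showing a difference of a clinically relevant size. This is the only justification given for the sample size on the primary outcome. It also bears on what a significant result may be said to show: the text pairs a clinical-superiority label and the minimal important difference with an analysis that names no margin.

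**Working it through.** **Inputs, all from the section above.** Difference 3 (cm on the VAS by context; the unit is not printed), SD 1.7 (variance 2.89), power 80% (Z = 0.842), alpha 0.05 (Z = 1.645 one-sided, as the printed Z₁₋α implies, or 1.960 two-sided).

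**1. Stated inputs, δ0 = 0.**
- One-sided: 2 × [(1.645 + 0.842)/3]² × 2.89 = 3.97, so 4 per group.
- Two-sided: 2 × [(1.960 + 0.842)/3]² × 2.89 = 5.04, so 6 per group.
- A t-based calculation gives 4.8 (5) and 6.2 (7).
- Reading S² as 1.7, as the key literally says, makes N smaller still: 2.3 or 3.0.

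None of these comes near 44. With δ0 = 0, a requirement of 44 would need an SD of about 5.7 (one-sided) or 5.0 (two-sided).

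**2. What gives 44.** Solving the one-sided formula for the denominator at N = 44 gives |δ − δ0| = 2.487 × 1.7 × √(2/44) = 0.90. The only other VAS distance in the paragraph is 3.9 cm, and 3 − 3.9 = −0.9:

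2 × [(1.645 + 0.842)/(3 − 3.9)]² × 2.89 = 44.1

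This matches the plan's figure, although strict rounding up would give 45. The two-sided version gives 56.0, or 57 rounded up. The denominator is negative, and squaring removes the sign.

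**3. Power with 44 per group.** The standard error is 1.7 × √(2/44) = 0.362.

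| Hypothesis tested | True difference | Power |
|---|---|---|
| Difference = 0, two-sided 5% | 3 | Φ(3/0.362 − 1.960) > 99.9% |
| Difference ≤ 3.9, one-sided 5% | 3 | Φ(−0.9/0.362 − 1.645) = Φ(−4.13) ≈ 0.002% |
| Difference = 0, two-sided 5% | 0.9 | Φ(0.9/0.362 − 1.960) ≈ 70% |

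The second row is conditional on 3.9 cm being the margin. When the true difference lies below the margin, more patients lower the power, so no sample size reaches 80%.

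**4. What the planned size supports.** For a two-sided 5% t test against zero with SD 1.7, the difference detectable with 80% power is:
- 44 analysed per group: 1.03 cm
- 42 analysed per group (53 × 0.8 = 42.4): 1.05 cm
- all 53 analysed: 0.93 cm

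**The case against.** **The origin of 44 is inferred.** A reader might conclude that 44 arises only if 3.9 cm was the margin, and that the trial can therefore essentially never succeed on its own terms. The document does not support stating that as fact. The formula depends only on the size of δ − δ0. An unprinted margin of 2.1 gives 3 − 2.1 = 0.9 and the same 44.1, with the effect above the margin and a valid one-sided 80% power. The text never says that the minimal important difference is δ0. It also explains clinical superiority as acupuncture being better than comfort needles, which can be read as ordinary superiority. This objection stands: 3.9 cm is the only printed figure that works, but the 0.002% is conditional on it.

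**The trial is not underpowered for its stated effect.** Also correct. Against zero, a true difference of 3 is detected almost with certainty. What fails is the justification of the number.

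**Sidedness and margin testing could sit in an analysis plan that is not shown.** This stands in part. The 70% figure assumes a two-sided test, which the text does not state, and an ANCOVA confidence limit can be compared with any margin. But the point does not rest on missing detail. The inputs, formula, key and result are all printed, and they disagree.

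**A detectable difference of about 1 cm is solved backwards from N.** True. It describes what the planned size can do; the document does not name it as a target or as a meaningful effect.

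**Conclusion.** The stated inputs do not produce the stated sample size: the printed formula gives 4 or 6 per group with δ0 = 0, against 44. δ0 has no value, and all three symbols δ, δ0 and S² are wrongly described, so the text cannot be used to repair the calculation. This part rests on the printed figures alone.

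The likely origin is the 3.9 cm minimal important difference entered as a margin larger than the expected effect, at a one-sided 5% level. That remains an inference, and the near-zero power for superiority beyond 3.9 cm holds only if it is right. For the two hypotheses that the printed figures allow, zero and 3.9 cm, power with 44 per group is above 99.9% and about 0.002%, so 80% describes neither. A significant ANCOVA against zero would not show superiority by the minimal important difference.

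The section is wrong as written and should be corrected. It does not show that 106 patients are too few.

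**What to change.** Keep 106 patients and rewrite the sample size paragraph:

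1. State the null hypothesis, the sidedness of the test and the value of δ0.
2. Define δ as the expected between-group difference, δ0 as the margin and S² as the variance. If the test is two-sided, use Z₁₋α/₂.
3. Restate the power. If the test is against zero at two-sided 5% with SD 1.7, say that 80% power holds for a difference of about 1.03 to 1.05 cm with 42 to 44 analysed per group (about 0.93 cm if all 53 are analysed), and that power for the stated 3 cm is near 100%.
4. If a clinical-superiority margin is intended, state one below the expected difference, recompute N, and compare the confidence limit from the ANCOVA with that margin. If none is intended, do not present a significant ANCOVA as superiority by the minimal important difference.

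For a test against zero the cost is wording only: no extra patients and no new endpoint, but a more modest claim. If a margin is chosen, whether 106 suffices depends on the recomputation. Whether to keep the clinical-superiority label is the sponsor's choice, provided that the hypothesis and the analysis match it.

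### The 20% dropout allowance multiplies 44 by 1.2 instead of dividing by 0.8, so 53 per group leaves about 42 completers, below the plan's own minimum of 44

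*Protocol article*

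**What the plan says.** The section Sample size calculations and statistical analysis ends its calculation with a floor: "So it requires each group to contain no less than 44 patients". The next sentence turns the floor into a recruitment target: "With an estimated 20% dropout rate, we plan to recruit 53 patients for each group, for a total of 106 patients".

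The total of 106 appears again in the Abstract, in Study design and in Randomization and blinding. No section defines the 20% in an unusual way or gives another rule for inflating the sample size.

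The inputs offered for the 44 are an SD ("assuming the standard deviation (SD) to be 1.7"), an expected difference ("the difference between two treatment effect to be 3"), 80% power and a 5% level ("the significance level is 0.05"). The formula also contains a margin, δ₀, to which no number is assigned.

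The same section plans intention-to-treat analysis, imputes missing data by last observation carried forward (LOCF), and removes participants who took analgesics from the analysis.

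**The concern.** A dropout rate is ordinarily a share of the patients enrolled. To keep n patients after losing a share d, one recruits n/(1 − d). Multiplying by (1 + d) adds back a share of the smaller number and always falls short: for d = 0.20 it retains 1.2 × 0.8 = 0.96 of the target, whatever the target is.

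The two adjacent sentences therefore cannot both hold: if 20% drop out, a group of 53 does not keep 44. What is at stake is the basis of the trial's recruitment total, which the article states in four places. A reader who takes 106 as protecting the stated minimum against the stated dropout is misled, though by little.

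**Working it through.** **Inputs**, all from Sample size calculations and statistical analysis: minimum 44 per group; dropout 20%; recruitment 53 per group, 106 in total; SD 1.7; expected difference 3; power 80%; level 0.05.

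**1. Reproduce the plan's figure.**
- 44 × (1 + 0.20) = 52.8, rounded up to 53. This matches the stated 53.
- 44 / (1 − 0.20) = 55. This does not match, and rounding cannot turn 55 into 53.

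**2. What 53 delivers at 20% dropout.**
- 53 × 0.80 = 42.4, so about 42 completers per group.
- 54 × 0.80 = 43.2, still below 44.
- 55 × 0.80 = 44.0, so 55 per group (110 in total) is the smallest number that meets the floor.

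**3. Dropout that 53 can bear.**
- 1 − 44/53 = 0.170, so about 17%.

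**4. Power, on the condition that 44 per group gives 80%.** With the SD and the difference to be detected held fixed, power at n per group is Φ[(z₁₋α + z₁₋β) × √(n/44) − z₁₋α], using z₁₋α/₂ for a two-sided test. The article does not say in words whether the test is one- or two-sided, and its formula uses the one-sided form, so both are shown for n = 42, where √(42/44) = 0.977.
- One-sided 5%: Φ[(1.645 + 0.842) × 0.977 − 1.645] = 78.4%.
- Two-sided 5%: Φ[(1.960 + 0.842) × 0.977 − 1.960] = 78.2%.

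Both are about 78%.

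**5. How firm is the 44?** The plan's formula is N = 2[(Z₁₋α + Z₁₋β)/(δ − δ₀)]² S².
- With δ = 3, δ₀ = 0 and S = 1.7, N is 4 per group (one-sided) or 6 (two-sided), rounded up.
- With |δ − δ₀| = 0.9 and a one-sided 5% level, N = 2 × (2.487/0.9)² × 2.89 = 44.1, that is 44 (45 if rounded up).

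The 0.9 is an inference. It is |3 − 3.9|, taking as δ₀ the 3.9 cm that the section reports as the minimal important difference. The article does not say that this was done. On that reading δ − δ₀ is −0.9: the expected difference lies below the margin, and squaring hides the sign. This is a separate and larger question about the base calculation. It matters here because every figure in steps 1 to 4 takes 44 as given.

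**The case against.** **Dropouts stay in the analysis.** This is the strongest objection. The plan is intention-to-treat with LOCF, the schedule in Table 2 records the VAS at inclusion and at every later visit, and randomization follows all baseline assessments. Every randomized patient should therefore have at least one VAS value, and dropping out does not by itself remove anyone from the analysis.

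This stands against a stronger reading that a reader might infer, namely that the trial will have only 42 analysable patients per group. The article does not support that. It does not rescue the 53, however. The authors chose to add patients for dropout, so they treated dropouts as a loss to be replaced, and the addition does not replace them. The article's one stated route out of the analysis is analgesic use. That would lower the number analysed, but it is not the 20% dropout.

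**The power loss is not established.** This also stands in part. A reader might infer that the trial falls from 80% to about 78% power as a fact. That holds only if 44 truly gives 80%. Against a zero margin, the stated difference of 3 with SD 1.7 needs only 4 to 6 per group, and power at 42 is practically 100%. With 3.9 as the margin, the expected effect lies on the wrong side of it. The 78% is conditional and should be labelled so.

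**The effect is small and the 20% is only an estimate.** Agreed. This limits the weight of the point but does not make the sentence correct, since the article's own estimate of 20% exceeds the 17% that 53 can bear.

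**Conclusion.** The point holds as an arithmetic error of minor size. The allowance uses × 1.2 where ÷ 0.8 is needed, so 53 per group leaves about 42 completers at the stated 20% dropout, below the stated minimum of 44. The gap is 2 per group and 4 in total (106 against 110), and 106 preserves 44 completers per group only up to about 17% dropout.

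It rests on three assumptions: that the 20% is a share of those recruited, since nothing in the article says otherwise; that the count concerns completers and not the LOCF analysis set; and that 44 is kept as the target. If the base calculation is redone, both 53 and 55 fall away, but the same multiplication would under-inflate the new number as well.

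**What to change.** Change one sentence in Sample size calculations and statistical analysis. Either of these is accurate at the present size:
- state that recruiting 53 per group (106 in total) yields about 42 completers per group if 20% drop out; or
- state that 106 patients preserve 44 completers per group for dropout up to about 17%.

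Use the word completers and not analysable, so that the sentence agrees with the intention-to-treat and LOCF plan. If a power is quoted for 42, mark it as conditional: about 78% if 44 per group gives 80%.

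If the sponsor prefers to keep both the 44 and the 20%, the matching figure is 55 per group, 110 in total, and the total then has to be changed in the Abstract, Study design, and Randomization and blinding as well. Before that choice, state the value of δ₀ and confirm the 44, because 55 is worth recruiting only if 44 stands.

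The restatement costs one sentence, a slightly less favourable claim and no extra patients. The enlargement costs 4 patients, and the article reports the trial as still recruiting.

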### Interventions

This study has two phases. The first phase will include 3 months of acupuncture treatment, and the second phase will include 3 months of follow-up without treatment. Patients will be randomly assigned to one of two groups in a 1:1 ratio, either the treatment group or the control group. Then, acupuncture treatment will start and last for 3 months following by 3 months of follow-up.

The whole acupuncture treatment will be carried out by two experienced acupuncturists who have received a license from the Ministry of Health of China and have practiced clinically for more than 5 years. Every acupuncture session will be once a day, three times a week and last for 30 min and only start from 7 days before the expected menstrual onset. During the menstrual period, they will receive acupuncture every day when they have endometriosis-associated pelvic pain.

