### Primary outcome

#### Pelvic pain

The primary outcome is pelvic pain that include dysmenorrhea, intermenstrual pain and dyspareunia. They will be assessed on a VAS scale [14]. On the VAS scale, a 100-mm horizontal line from no pain on the far left to the worst possible pain on the far right is scored by determining the distance from the far left to the edge of the mark made by the patient. The distance represents pain intensity. The VAS will be assessed at baseline, the first, second and third menstrual cycles and the follow-up period. See Table 2 for the study design schedule.

**Table 2 Tab2:** Study design schedule

Period	Inclusion	Treatment			Follow-up		
Visit	1	2	3	4	5	6	7
Menstrual cycle	0 month	1	2	3	4	5	6
Patients	√						
Inclusion and exclusion criteria	√						
Informed consent	√						
Physical examination	√			√			
Medical history	√						
Comorbidities	√	√	√	√	√	√	√
VAS	√	√	√	√	√	√	√
EHP-30	√			√			√
MPI	√			√			√
BDI and POMS	√			√			√
PGIC	√			√			√
Pain diary	√	√	√	√	√	√	√
Patient compliance				√			√
Reasons for dropout or withdrawal				√			√
Adverse events				√			
Safety evaluation							√

*BDI* Beck Depression Inventory, *EHP* Endometriosis-specific quality of life, *MPI* Multidimensional Pain Inventory, *PGIC* Patient Global Impression of Change, *POMS* Profile of Mood States, *VAS* Visual Analog Scale

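### LOCF is the only missing-data rule for every visit, so on-treatment pain scores can be carried into the untreated follow-up and can create apparent durability if the effect has waned

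*Protocol article*

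**What the plan says.** The section Sample size calculations and statistical analysis states the rule: "Missing data will be imputed according to the last-observation-carried-forward (LOCF". Nothing restricts it to a phase, a visit, an outcome or a sensitivity analysis, and the article names no other method for missing data. The same section adds "The data will be subjected to intent-to-treat analysis" and "The between-group difference will be compared by analysis of covariance", with a rank-sum test for non-normal variables. It allows for 20% dropout and recruits 53 per group.

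On timing, the Pelvic pain section says "The VAS will be assessed at baseline, the first, second and third menstrual cycles and the follow-up period". Table 2 puts the VAS at visit 1 (baseline), visits 2 to 4 (cycles 1 to 3, treatment) and visits 5 to 7 (cycles 4 to 6, follow-up). Under Interventions, "the second phase will include 3 months of follow-up without treatment". The Follow-up section gives its purpose: "The goal of follow-up is to evaluate the long-term efficacy of acupuncture on pain relief".

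In Table 2 the EHP-30, MPI, BDI, POMS and PGIC are scheduled only at baseline, cycle 3 and cycle 6.

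**The concern.** LOCF assumes that a patient's score would have stayed where it was when last seen. In this design that assumption crosses a change of condition: needling stops after cycle 3. Carrying a cycle 3 score to cycle 6 therefore presumes that the treatment effect lasts three cycles without treatment, which is the question follow-up asks. If the effect fades, the carried scores pull the cycle 6 comparison towards persistence.

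The questionnaires are more exposed than the VAS. With no measurement between cycle 3 and cycle 6, the value carried to cycle 6 is the end-of-treatment score or, failing that, the baseline score. No off-treatment value exists to carry.

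The second problem is precision. A carried score enters the analysis of covariance as if it had been observed, so the loss of information from missing data need not show in the standard error.

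**Working it through.** **Inputs from the protocol article.** SD 1.7 and between-group difference 3 ("assuming the standard deviation (SD) to be 1.7 and the difference between two treatment effect to be 3", read here as cm on the VAS); dropout 20%; 53 per group; significance level 0.05, tested two-sided here. The recruitment figure follows from the dropout allowance: 44 × 1.2 = 52.8, so 53. How the 44 was derived is a separate matter and does not enter this check.

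**Assumptions not in the article.** The true difference at cycle 6 is zero; the end-of-treatment effect is 1 to 3 cm; dropout is equal between arms and unrelated to outcome; its timing is as stated in each case. The simulations also assume correlation 0.5 between visits.

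**Step 1: bias.** Spurious difference = share of patients whose last score is on treatment × effect at that time.
- 20% lost at end of treatment: 0.2 × 1 = 0.2 cm; 0.2 × 3 = 0.6 cm.
- 10% lost there and nothing else carried: 0.1 × 1 = 0.1 cm; 0.1 × 3 = 0.3 cm.
- 20% with last scores spread evenly over cycles 1 to 5, effects 1, 2, 3, 2, 1 cm: 0.2 × (9/5) = 0.36 cm.

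**Step 2: false-positive rate.** SE = 1.7 × √(2/53) = 0.330. Rejection rate = Φ(b/SE − 1.96) + Φ(−b/SE − 1.96).

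| Share lost at end of treatment | Effect 1 cm | Effect 3 cm |
|---|---|---|
| 20% | b = 0.2: 9.3% | b = 0.6: 44.3% |
| 10% | b = 0.1: 6.1% | b = 0.3: 14.9% |

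**Step 3: is this SE right for the planned analysis?** It ignores the gain from baseline adjustment and also the extra spread from mixing carried and observed scores in the acupuncture arm. With both included, the variance is 1.7²(1 − ρ²) + p(1 − p)e²/2, where p is the share lost, e the effect and ρ the correlation with baseline. For p = 0.2 and e = 3:
- ρ = 0: 2.89 + 0.72 = 3.61, SE 0.369, rejection 37%.
- ρ = 0.5: 2.1675 + 0.72 = 2.8875, SE 0.330, rejection 44%.
- ρ = 0.7: 1.4739 + 0.72 = 2.1939, SE 0.288, rejection 55%.

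So 44% is the value near ρ = 0.5. At ρ = 0.5 the other three cells become 11% (20%, 1 cm), 6% (10%, 1 cm) and 16% (10%, 3 cm).

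**Step 4: simulation of the planned ANCOVA** (4,000 runs, 53 per arm, 20% dropout per arm; negative favours acupuncture).

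| Scenario | True difference at cycle 6 | LOCF estimate | LOCF rejection | Observed-score estimate | Observed-score rejection |
|---|---|---|---|---|---|
| 3 cm effect, waned; cycle 3 carried | 0 | −0.61 | 44% | −0.01 | 4.8% |
| 1.5 cm effect, waned; cycle 3 carried | 0 | −0.30 | 16% | 0.01 | 5.2% |
| 3 cm effect, waned; last score in cycles 1 to 5 | 0 | −0.36 | 21% | 0.00 | 4.7% |
| No effect, stable means; cycle 3 carried | 0 | 0.00 | 4.5% | 0.00 | 5.1% |
| 3 cm effect, sustained; last score at baseline to cycle 2 | −3 | −2.60 | 100% | −3.00 | 100% |

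The last row agrees with arithmetic: 0.8 × 3 + 0.2 × (0 + 1 + 2)/3 = 2.6.

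**Step 5: standard error.** With stable means the LOCF SE is 0.287, the same to within 0.001 as with complete data on all 106 patients, against 0.322 from the scores actually observed: 1 − 0.287/0.322 = 0.11. In the 3 cm waning case the LOCF SE is 0.331, which is not below 0.322; there the failure is bias.

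**The case against.** Three stronger readings are tempting, and the article does not support them.

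First, a reader might infer that LOCF will produce a false claim of durability. That needs both a waning effect and losses after benefit has been gained. The article establishes neither. If the effect persists and patients leave early, LOCF works against acupuncture; with stable means and equal dropout it is unbiased.

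Second, a reader might take 44% as the error rate of the trial. It is the rate for the cycle 6 comparison when all 20% of losses fall at the end of treatment and a 3 cm effect has gone completely. The 20% is an overall recruitment allowance with no split by phase, and patients may send follow-up information by email or short message, so heavy loss at that point is not evident. Nor does the figure describe the main efficacy test: no error is quantified for the treatment phase, where the direction of LOCF bias depends on who leaves and when.

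Third, a reader might infer that the standard error is always too small. That holds when means are stable, but not in the waning case behind the largest figure.

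These objections limit the size of the point and leave its core intact. Whether LOCF is harmless here depends on facts that the sponsor cannot know in advance. Two general defences also fall short. Intention-to-treat does not require single imputation, because a mixed model keeps every patient with a post-baseline score. And LOCF is not conservative when an effect fades after treatment stops.

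**Conclusion.** The point holds as a recommended change. The article itself fixes LOCF for all visits, so this is a stated choice and not a detail left to an unseen analysis plan. In an untreated follow-up meant to assess lasting benefit, the rule can supply the persistence it should be testing.

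If no effect is left at cycle 6, the spurious difference runs from 0.1 cm (10% lost at end of treatment, 1 cm effect) to 0.6 cm (20%, 3 cm), and the false-positive rate from about 6% to about 44%. Spreading the losses over cycles 1 to 5 with a 3 cm effect gives about 0.36 cm and 21%. These figures rest on assumed timing, complete washout and equal dropout unrelated to outcome. The simulated ones, and the agreement of the simple SE with the planned ANCOVA in the 3 cm case, also rest on correlation 0.5. The understatement of the SE, about 11%, applies to stable means under the same correlation.

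**What to change.** For the VAS, replace LOCF with a mixed model for repeated measures on all observed post-baseline scores at visits 2 to 7, with baseline VAS, arm, visit and arm-by-visit terms. Report the end-of-treatment contrast (visit 4) and the cycle 6 contrast (visit 7). Which time point is primary is a separate matter that this change does not settle.

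Because the model assumes data missing at random, add a control-based multiple-imputation sensitivity analysis, in which acupuncture patients who withdraw are imputed from the control arm's course.

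For every outcome, state that on-treatment values are not carried into cycles 4 to 6. Keep LOCF, if at all, as a sensitivity analysis for the treatment phase only.

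The cost is a change of wording in the analysis plan and slightly more programming. The VAS is already scheduled at every visit, and the article reports the trial as still recruiting. The price in precision is a somewhat wider SE than LOCF shows when means are stable, which reflects the data actually collected.
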